### Subjects

Based on a power calculation (see 2.6), we aim to recruit 1,000 patients, 500 in each of the two treatment arms. Recruitment is primarily based on self-referral, including referrals from general practice, hospitals etc., to the treatment facilities. All patients aged 60 years or older who ask for treatment are informed that this project is being conducted and are recruiting participants. If a person up front is not interested in the study this person receives standard treatment according to local guidelines. If the person is interested, a session with a research assistant is set up. The person (and family members or significantly others if the person wants support or discussing the implications of participating before deciding) receives oral and written for information about the study. There is no time limit for potential participants to decide whether to participate or not, and the potential participant may return to the research group with questions before deciding to participate or not. No project procedures are conducted before a signed informed consent, which may be revoked at any time if the participant regrets participation. We strive for ecological validity and only exclude patients who are unable to participate in the therapy or are suffering from severe conditions judged to threaten their safety or the validity of the study. *Inclusion criteria:* (1) Older adults (≥60 years) with an (2) alcohol use disorder according to DSM-5 [31] and (3) before participation pass 8 out of 10 questions in a comprehension quiz pertaining to the implications of participating in the study, for example knowledge about voluntary participation and that any acceptance of participation can be withdrawn at any time. This custom-made quiz is conducted after informed consent, and is in a multiple-choice format. *Exclusion criteria:* (1) Current psychotic symptoms (2) Severe depression at the time of screening. (3) Manic episode in the last three months prior to screening or lifetime diagnosis of bipolar disorder. (4) Suicidal thoughts/behaviour at the time of screening. (5) Use of illicit opioids and/or illicit stimulants (*all other forms of medication is allowed, including opioids by prescription*). (6) Participating or having participated in other alcohol treatment programs in the last 30 days at the time of screening. Pure detoxifications are not exclusionary. (7) Patients with legally authorized representatives.

### Interventions

#### Brief MET treatment (Standard treatment)

Consists of 4 sessions, 1 per week. The intervention is based on the initial phases of the Combined Behavioral Intervention (CBI) from Project COMBINE [32, 33], and includes motivational interviewing, a functional analysis and planning for change as appropriate. In this condition, the change plan focuses exclusively on self-directed activities both during the treatment and after the 4 sessions are completed. A concerned significant other (CSO) may participate in the last session.

#### Extended treatment

Consists of 4 initial sessions similar to those in the Brief MET Treatment, except that the change plan is explicitly designed to include therapeutic modules to be completed collaboratively with the therapist. Similarly to the Brief MET Treatment, a CSO can be included in session 4. After the first 4 sessions, up to 8 additional sessions can be used by the therapist and client to implement the change plan with 1 session per week. This is accomplished through modules addressing specific areas pertaining to older age alcohol use disorders, which are together called CRA for Seniors (CRAS-S). CRAS-S consists of 5 independent modules: 1) Coping with Craving, Urges, and Social Pressure to Drink; 2) Coping with Aging; 3) Mood Management Training; 4) Building a Sober Network; and 5) Social and Recreational Counselling. These modules are based on the manual and procedures for the Combined Behavioural Intervention (CBI) as developed and tested in the COMBINE trial. Unique to this intervention, a module to manage the challenges of aging has been developed. This module, Coping with Aging, addresses older adults’ needs and problems with strategies for coping with aging and attendant losses. Formulated to encompass the 5 domains from the Happiness Form, the module on aging is adapted to the style and procedures of CRA (Table 1). Based on the change plan, the relevant topics/modules for treatment are chosen by participant and therapist. Thus the manual consists of standardized modules with detailed descriptions of the content and procedures for each module, but flexibility to allow the therapist and client to choose which modules are relevant for patient’s problem profile. The selection and order of modules and how many sessions devoted to each module is planned collaboratively, and sessions typically include more than one module at a time.

**Table 1 Tab1:** Personal happiness form, adapted from the combine study [33]

Personal happiness form															
	How happy or satisfied are you with each of these areas of your life? (circle only one number for each item)											If unsatisfied, (= < 5), what is the reason? Please mark more than one if appropriate*			
Life areas	Completely dissatisfied		Somewhat dissatisfied		Somewhat satisfied		Mostly satisfied		Completely satisfied		Doesn’t apply (IR)	Loss	Loneliness	Loss of ability due to aging	Something else, please note
Growing old*	1	2	3	4	5	6	7	8	9	10	IR	0 = no	0 = no	0 = no	
												1 = yes	1 = yes	1 = yes	
												9 = irr.	9 = irr.	9 = irr.	
Inter personal relations															
Relationship with partner/spouse	1	2	3	4	5	6	7	8	9	10	IR	0 = no	0 = no	0 = no	
												1 = yes	1 = yes	1 = yes	
												9 = irr.	9 = irr.	9 = irr.	
Friends and social life	1	2	3	4	5	6	7	8	9	10	IR	0 = no	0 = no	0 = no	
												1 = yes	1 = yes	1 = yes	
												9 = irr.	9 = irr.	9 = irr.	
Family relationships	1	2	3	4	5	6	7	8	9	10	IR	0 = no	0 = no	0 = no	
												1 = yes	1 = yes	1 = yes	
												9 = irr.	9 = irr.	9 = irr.	
Love and affection	1	2	3	4	5	6	7	8	9	10	IR	0 = no	0 = no	0 = no	
												1 = yes	1 = yes	1 = yes	
												9 = irr.	9 = irr.	9 = irr.	
Sex life	1	2	3	4	5	6	7	8	9	10	IR	0 = no	0 = no	0 = no	
												1 = yes	1 = yes	1 = yes	
												9 = irr.	9 = irr.	9 = irr.	
Social life															
Leisure time and fun	1	2	3	4	5	6	7	8	9	10	IR	0 = no	0 = no	0 = no	
												1 = yes	1 = yes	1 = yes	
												9 = irr.	9 = irr.	9 = irr.	
Giving/caring for others	1	2	3	4	5	6	7	8	9	10	IR	0 = no	0 = no	0 = no	
												1 = yes	1 = yes	1 = yes	
												9 = irr.	9 = irr.	9 = irr.	
Personal safety, security	1	2	3	4	5	6	7	8	9	10	IR	0 = no	0 = no	0 = no	
												1 = yes	1 = yes	1 = yes	
												9 = irr.	9 = irr.	9 = irr.	
Life circumstances															
Job/work/pension	1	2	3	4	5	6	7	8	9	10	IR	0 = no	0 = no	0 = no	
												1 = yes	1 = yes	1 = yes	
												9 = irr.	9 = irr.	9 = irr.	
Where I live	1	2	3	4	5	6	7	8	9	10	IR	0 = no	0 = no	0 = no	
												1 = yes	1 = yes	1 = yes	
												9 = irr.	9 = irr.	9 = irr.	
Money, financial security	1	2	3	4	5	6	7	8	9	10	IR	0 = no	0 = no	0 = no	
												1 = yes	1 = yes	1 = yes	
												9 = irr.	9 = irr.	9 = irr.	
Physical health															
Physical health	1	2	3	4	5	6	7	8	9	10	IR	0 = no	0 = no	0 = no	
												1 = yes	1 = yes	1 = yes	
												9 = irr.	9 = irr.	9 = irr.	
Physical activities, exercise	1	2	3	4	5	6	7	8	9	10	IR	0 = no	0 = no	0 = no	
												1 = yes	1 = yes	1 = yes	
												9 = irr.	9 = irr.	9 = irr.	
Daily routine, the small tasks during the day	1	2	3	4	5	6	7	8	9	10	IR	0 = no	0 = no	0 = no	
												1 = yes	1 = yes	1 = yes	
												9 = irr.	9 = irr.	9 = irr.	
Eating, weight	1	2	3	4	5	6	7	8	9	10	IR	0 = no	0 = no	0 = no	
												1 = yes	1 = yes	1 = yes	
												9 = irr.	9 = irr.	9 = irr.	
Psychological health															
Mood and self-esteem	1	2	3	4	5	6	7	8	9	10	IR	0 = no	0 = no	0 = no	
												1 = yes	1 = yes	1 = yes	
												9 = irr.	9 = irr.	9 = irr.	
Stress and anxiety	1	2	3	4	5	6	7	8	9	10	IR	0 = no	0 = no	0 = no	
												1 = yes	1 = yes	1 = yes	
												9 = irr.	9 = irr.	9 = irr.	
Anger and arguments	1	2	3	4	5	6	7	8	9	10	IR	0 = no	0 = no	0 = no	
												1 = yes	1 = yes	1 = yes	
												9 = irr.	9 = irr.	9 = irr.	
Spirituality	1	2	3	4	5	6	7	8	9	10	IR	0 = no	0 = no	0 = no	
												1 = yes	1 = yes	1 = yes	
												9 = irr.	9 = irr.	9 = irr.	
Memory	1	2	3	4	5	6	7	8	9	10	IR	0 = no	0 = no	0 = no	
												1 = yes	1 = yes	1 = yes	
												9 = irr.	9 = irr.	9 = irr.	
Mental ability	1	2	3	4	5	6	7	8	9	10	IR	0 = no	0 = no	0 = no	
												1 = yes	1 = yes	1 = yes	
												9 = irr.	9 = irr.	9 = irr.	

*Added a question about aging in general and if dissatisfaction in any domain is reported, then is it because of factors related to aging

### Instruments and measurement

Patients will be assessed at screening, at baseline, at the end of MET treatment (4 weeks after baseline), at the end of MET + CRA treatment (12 weeks after baseline), at six months after baseline (the time of primary outcome), and at 12 months after baseline (See Table 2).

**Table 2 Tab2:** The evaluation instruments

Assessment	Purpose/Content	BL	Wk 4	Wk 12	Wk 26	Wk 52
Alcohol consumption, dependence, and criteria for AUD						
Form 90-AI/F [38]	Primary outcome: daily alcohol use	•	•	•	•	•
Alcohol Dependence Scale [39, 47]	Alcohol Dependence	•			•	•
Drinker Inventory of Consequences [48]	Adverse consequences of drinking	•	•	•	•	•
Mini-International Neuro-psychiatric interview [34]	Module J: Assess whether the patient continuously fulfil the DSM-5 criteria for AUD	•	•	•	•	•
Motivation						
Importance, Confidence, Readiness [49] (3 Likert scales)	Change in motivation	•	•	•	•	•
Craving						
Penn Alcohol Craving Scale [40]	Changes in craving	•	•	•	•	•
Alcohol Abstinence Self-Efficacy Scale T/C [41]	Changes in self-efficacy	•	•	•	•	•
Psychological and Psychiatric assessment						
Brief Symptom Inventory 18 [36]	Changes in anxiety, depression etc.	•	•	•	•	•
Quality of life, domains with problems related to aging						
WHOQOL-BREF [42]	Changes in quality of life	•	•	•	•	•
Personal Happiness Form [33]	Identifying and assessing changes in interpersonal relations (family, friends, etc), life circumstances (housing, work/retirement, etc.), physical and psychological health	•	•	•	•	•
Therapy Compliance and Treatment Satisfaction						
Questionnaire on “Goal of treatment”	Questions on what the patients wants from treatment	•				
Session Record Form^a^	Quality control	•	•	•		
Treatment Satisfaction Form	Patients’ evaluation of treatment		•	•	•	•
Hair sample of 10 % of patients	Measuring alcohol to assess alcohol consumption the last 30 days				•	

BL: Baseline

Wk: week

^a^Completed after every session during MET- and CRA-treatment, week 1–12

*Screening* includes Modules J (alcohol), A (depression), D (manic episode), and L (psychosis) of the Mini-International Neuro-psychiatric Interview (M.I.N.I.) (version 5.0.0) to assess inclusion and exclusion criteria [34]. To comply with the DSM-5 criteria for alcohol use disorder two questions on craving have been added in module J of the M.I.N.I. [35].

### Outcome measures and hypotheses

#### Primary outcome

Proportion of patients with abstinence or controlled use (maximum alcohol resulting in an estimated BAC ≤ 0.05 %) in the last 30 days at 6 months after start of treatment.

Although “controlled use” is included as a positive outcome in the primary outcome analysis, secondary analyses will examine total abstinence as a treatment outcome. In the program, the therapist as a treatment goal recommends abstinence. However, participants who are unwilling to become abstinent are supported in achieving a reduction of their alcohol use.

#### A priori hypotheses

Patients randomly assigned to a brief outpatient behavior therapy program (MET; Treatment Group 1) will show a significant improvement of their drinking pattern between onset, end of treatment and 6- and 12-month follow-up.Patients randomly assigned to a more intensive outpatient behavior therapy (MET plus CRA; treatment group 2) will show a significant *greater* improvement of their drinking pattern between onset, end of treatment and 6- and 12-month follow-up than treatment group 1. A clinically significant difference in outcome is defined as at least a 10 %-points greater rate of abstinence or drinking in a controlled manner in treatment group 2 compared to group 1.

#### Secondary outcomes

Proportion of total abstinence in each treatment group at 6-month follow-upPercentage of patients with abstinence or controlled use (maximum daily alcohol intake equivalent to BAC ≤ 0.05 %):In the last 7 days before regular end of treatment (end of MET and end of MET + CRA, respectively)In the last 30 days at 12 month follow-upQuality of lifeThe proportion of clients completing the planned treatment

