### Statistical analyses

Multiple logistic regression models will be used to analyse primary and secondary outcomes, and explanatory variables will include treatment, site, gender and age as well as other relevant demographic variables. The statistical analyses will be based on an “intent-to-treat”-approach, thus all patients randomized to treatment will be included. A multiple imputation strategy will be used in case of missing explanatory variables. The primary hypothesis of differences between treatment conditions will be tested one-sided since MET + CRA treatment is an extension of MET treatment. All other hypotheses will also be tested one-sided. In addition, we will perform a participation analysis where a logistic regression analysis is used to investigate how available demographics characteristics affect the probability that an individual will accept participation in the study.

The primary outcome is abstinence *or* controlled use as stated above. Information from the Form-90 is used to calculate the BAC based on the Widmark formula with an age adjustment [43].

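### The end-of-treatment drinking outcome is most naturally read at week 4 in the MET arm and week 12 in the MET + CRA arm, so its between-arm comparison mixes treatment with time

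*Protocol article*

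**What the plan says.** Under Secondary outcomes, the protocol article defines abstinence or controlled use at two further occasions. One is the last 30 days at 12 months. The other is "In the last 7 days before regular end of treatment (end of MET and end of MET + CRA, respectively"). Instruments and measurement supplies the dates of the two ends of treatment: "at the end of MET treatment (4 weeks after baseline), at the end of MET + CRA treatment (12 weeks after baseline").

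The statistical section states that "Multiple logistic regression models will be used to analyse primary and secondary outcomes", lists treatment among the explanatory variables, and adds: "All other hypotheses will also be tested one-sided". The second a priori hypothesis, that MET + CRA improves drinking more than MET alone, names end of treatment alongside the 6- and 12-month follow-ups.

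Table 2 marks Form-90, the source of daily alcohol use, at baseline and at weeks 4, 12, 26 and 52, with no distinction by arm.

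The list of secondary outcomes also includes the proportion who complete their planned treatment. In the MET arm the plan "Consists of 4 sessions, 1 per week". In the extended arm, four similar sessions are followed by a variable number: "up to 8 additional sessions can be used by the therapist and client to implement the change plan with 1 session per week".

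**The concern.** Randomisation makes the arms comparable at the same time after baseline. Here the time of reading is set by the arm: week 4 for all MET patients and week 12 for all MET + CRA patients. Arm and time since baseline are then completely aliased. Site, gender, age and the other demographic variables in the model are baseline features, and none of them carries information about what happens between weeks 4 and 12. Adjustment cannot repair the comparison.

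At stake is the only between-arm drinking comparison the plan defines around the end of treatment. If drinking worsens after the first month, the comparison penalises MET + CRA for being read later. If drinking is still improving, it credits MET + CRA with time alone. A one-sided test reacts very differently to these two cases: the first makes rejection almost impossible, and the second makes a false positive likely.

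**Working it through.** **1. The plan's own figure.** Inputs from Power calculation: 50 % versus 60 %, one-sided 5 %, power 90 %. The pooled two-proportion formula without continuity correction gives 423 per group, as stated. Allowing for 15 % dropout, 423 / 0.85 = 498, which the protocol rounds to 500. This calculation uses the six-month outcome, so the present point does not touch it.

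**2. Times of reading.** MET: week 4. MET + CRA: week 12. The difference is 8 weeks = 56 days.

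**3. A drift that fits the protocol's expectations.** The document gives no success rate at week 4 or week 12. Assume 60 % at week 4 in both arms, no treatment effect, and a constant proportional decline to the 50 % that the protocol expects for MET at six months (week 26). The difference between the 7-day and 30-day windows is ignored.
- Week 4 to week 26: 154 days = 154 / 30.4 = 5.07 months.
- Monthly loss: 1 − (50/60)^(1/5.07) = 3.5 %.
- Rate at week 12: 0.60 × (50/60)^(56/154) = 0.562.
- Artefact: 60.0 − 56.2 = 3.8, or about 4 points against MET + CRA.

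**4. Effect on the one-sided test.** Take no treatment effect, n = 500 per arm, MET read at rate p1 (week 4) and MET + CRA read at p2 (week 12), which differs from p1 only through time. With p̄ = (p1 + p2)/2:

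SE0 = √[2 p̄(1 − p̄)/n], SE1 = √[(p1(1 − p1) + p2(1 − p2))/n], P(reject) = Φ{[(p2 − p1) − 1.645 × SE0] / SE1}.

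For a rise from 50 % to 55 %: SE0 = 0.03158, SE1 = 0.03154, and (0.05 − 0.05195) / 0.03154 = −0.062, so P = 0.475. For a fall from 50 % to 45 % the standard errors are the same, and (−0.05 − 0.05195) / 0.03154 = −3.23, so P = 0.0006.

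| Assumed change, week 4 to 12, from 50 % | One-sided rejection, 500 per arm | 423 per arm |
|---|---|---|
| −5 points | 0.06 % | 0.1 % |
| 0 | 5 % | 5 % |
| +3 points | 24 % | 22 % |
| +5 points | 48 % | 43 % |
| +10 points | 94 % | 90 % |

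Reading both arms at the same week removes the drift from the contrast and returns the rejection rate under no effect to 5 %, whatever the drift.

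**The case against.** **Both visits may be meant for everyone.** Instruments and measurement uses nearly the same phrases as visit labels that apply to all patients, and Table 2 collects Form-90 from both arms at both weeks. The outcome could then mean week 4 and week 12 for every patient. This reading is possible but less natural. Week 4 is not the regular end of treatment for a MET + CRA patient, and the closing word of "In the last 7 days before regular end of treatment (end of MET and end of MET + CRA, respectively") pairs each end with its arm. If both visits were intended, the sentence should say so.

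**The modelling sentence is generic.** It covers all primary and secondary outcomes, including quality of life, and details may sit in an analysis plan that is not shown. That is fair as to the model. The time of reading, however, is part of the outcome definition, which this document fixes, and the between-arm hypothesis names end of treatment.

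**Length is part of the intervention.** True, and a common-week comparison respects it: at week 12, MET patients have been out of treatment for eight weeks, which is a legitimate part of the contrast.

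**Stronger readings the documents do not support.**
- A reader might infer that the artefact reaches the trial's 10-point clinical threshold. A loss of 10 % of successes per month from 60 % at week 4 does give 0.60 × 0.90^(56/30.4) = 49.4 % at week 12, a gap of 11 points. Carried on to week 26, the same rate gives 35 %, well below the 50 % or more that the protocol expects for MET.
- A reader might infer that the completion outcome is equally flawed. It is a legitimate measure of compliance, and no hypothesis is stated about it. With 95 % retention per session in both arms, 0.95^4 = 81 % and 0.95^12 = 54 %, a 27-point gap. That assumes everyone plans all 12 sessions, while the protocol says "up to 8 additional sessions can be used by the therapist and client" and leaves the use of sessions to joint planning. At a given retention, 12 sessions is the upper limit of the gap.
- A reader might infer that the whole between-arm hypothesis rests on this outcome. It is one of several time points named, and the 10-point difference is powered at six months.

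**Conclusion.** The point holds for one secondary outcome, on the more natural reading of its definition. As written, the end-of-treatment comparison cannot be interpreted as a treatment effect, because time since baseline differs by arm and cannot be adjusted away.

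The size is not known from the document. About 4 points against MET + CRA follows from an assumed 60 % at week 4 and a constant decline to the protocol's 50 % at six months. The rejection rates of about 48 % and below 0.1 % follow from assumed changes of +5 and −5 points from 50 %. The direction could be either.

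Only secondary inference is affected. The primary outcome, 6-month abstinence and the 12-month outcome are read at common times, and the sample size reproduces. Completion of planned treatment can stay as a per-arm description, but a between-arm difference in it is not a like-for-like comparison, because planned length is 4 sessions in one arm and 4 plus up to 8 in the other.

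**What to change.** Redefine the outcome as abstinence or controlled use in the last 7 days at week 12 after baseline, and also at week 4, in all randomised patients of both arms. State which of the two is the main end-of-treatment comparison. Week 12 is the more informative, since up to week 4 both arms receive four similar sessions.

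For completion, report the proportion in each arm with the number of sessions planned and attended, and state that the difference between arms is not a like-for-like comparison.

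The cost is the rewording of one outcome and a sentence on another. No visit, instrument or patient is added, because Form-90 is already scheduled at both weeks without a split by arm.

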### Statistical analyses

Multiple logistic regression models will be used to analyse primary and secondary outcomes, and explanatory variables will include treatment, site, gender and age as well as other relevant demographic variables. The statistical analyses will be based on an “intent-to-treat”-approach, thus all patients randomized to treatment will be included. A multiple imputation strategy will be used in case of missing explanatory variables. The primary hypothesis of differences between treatment conditions will be tested one-sided since MET + CRA treatment is an extension of MET treatment. All other hypotheses will also be tested one-sided. In addition, we will perform a participation analysis where a logistic regression analysis is used to investigate how available demographics characteristics affect the probability that an individual will accept participation in the study.

The primary outcome is abstinence *or* controlled use as stated above. Information from the Form-90 is used to calculate the BAC based on the Widmark formula with an age adjustment [43].

#### Power calculation

The number of patients is based on a power calculation with an expectation that at least 50 % of patients in MET treatment and 60 % of patients in the MET + CRA will have a good clinical outcome six months after treatment initiation as defined above in primary outcome. Since MET + CRA is an extension of MET, we will employ 1-sided hypothesis testing. With a significance level of 5 % (one-sided) and a power of 90 % each treatment group, MET and MET + CRA, will require 423 patients. As we foresee a dropout rate at approximately 15 %, we will strive for 500 patients in each group.

